**Secondary outcomes**								
	Therapeutic Inertia	Provider adherence to KDIGO^c^ goals: Timely medication changes (date of medication change following medication adherence) and BP feedback (biweekly SMASK^d^ reports for SMASK participants) and from clinic visits for all subjects (Figure 2)	Weekly^e^	Weekly^e^	Weekly^e^	Weekly^e^	Weekly^e^	Weekly^e^
	Self Determination Theory Constructs	TSRQ^f^ autonomous self-regulation [51,52] (α=0.81-0.84; correlation with GCOS^g^: *r*=0.38, *P*<.001; correlation with HCCQ^h^: *r*=0.38, *P*<.001), weight loss attendance (*r*=0.34, *P*<.001), body mass index (*r*=-0.11, *P*<.05), 18-month test-retest autonomous (*r*=0.47), controlled items (*r*_s_=0.34]) [53], correlation with medication adherence (*r*=0.58, *P*<.001)] [54]	✓			✓	✓	✓

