### Recruitment

Eligible patients were identified from hospital medical records by a research assistant. A research coordinator approached potential subjects in the kidney transplant clinic and obtained voluntary informed consent from patients who were interested in participating. After obtaining informed consent, the clinic resting BP protocol was conducted (see Clinic Resting Blood Pressure) and if SBP ≥130 mm Hg, the subject completed a set of questionnaires (Table 1) and was instructed to wear a SpaceLabs 90207 ambulatory BP monitor (SpaceLabs, Inc, Issaquah, WA) for 24 hours. The subject then began the 1-month screening period, as described above. The study site performs approximately 20 kidney transplants per month. We provide a smartphone and an internet data plan for the SMASK subjects who do not own a smartphone compatible with the SMASK app.

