#### Secondary Outcome Measures

Secondary outcome measures of changes in self-determination theory tenants (self-efficacy and autonomous self-regulation) and provider adherence to KDIGO guidelines (timing of medication changes) will be investigated using mixed effects models with these outcomes as separate dependent variables, group (SMASK vs SC) as primary independent variable, and the primary outcomes (medication adherence and clinic SBP) and clinical and demographic characteristics as adjustment variables.

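### The secondary model for changes in the self-determination constructs does not list the construct's own screening score as a covariate, which costs precision if the change is analysed unadjusted

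*Protocol article*

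**What the plan says.** Under Statistical Analyses, Secondary Outcome Measures, the protocol article names as outcomes the "Secondary outcome measures of changes in self-determination theory tenants (self-efficacy and autonomous self-regulation" pair, together with provider adherence to guidelines. These "will be investigated using mixed effects models with these outcomes as separate dependent variables". The terms listed are "group (SMASK vs SC) as primary independent variable, and the primary outcomes (medication adherence and clinic SBP) and clinical and demographic characteristics as adjustment variables". No pre-randomisation score of the construct appears in that list.

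The score is scheduled. In Table 1 the row for the self-determination constructs, which names the Treatment Self-Regulation Questionnaire (TSRQ), is ticked at screening and at 3, 6 and 12 months. The Recruitment section confirms that a patient with a qualifying blood pressure completed the Table 1 questionnaires before the one-month screening period, and so before randomisation. The same row reports "18-month test-retest autonomous (*r*=0.47") for the TSRQ.

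The article gives no effect size, standard deviation or power for any secondary outcome, and no retest correlation for self-efficacy.

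**The concern.** A questionnaire score measured before randomisation is usually among the best predictors of the same score later. A change score does use the screening value, but with a fixed weight of one. When the correlation between the two occasions is modest, that weight is too large. Below a correlation of 0.5, subtracting the screening score even adds more variance than it removes. Entering the score as a covariate lets the data choose the weight.

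Change in these constructs belongs to the second of the trial's two stated aims, and the Discussion presents them as the route to sustained adherence. With 40 patients per arm, a real effect on motivation is more likely to be missed if the analysis is less precise than the collected data allow. Randomisation is stratified by race and gender only, so a chance imbalance in screening motivation would also carry over into the change scores of that particular sample.

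**Working it through.** **The plan's own figure.** There is none for these outcomes. The only power statement (Proposed Sample Size: 40 per group, two-sided 0.05, more than 90% power for a 35-point difference) concerns the binary primary outcomes. It reproduces at 89.4% for a control rate of 0.325, the least favourable case, and at about 99% for a control rate of 0. It does not bear on the secondary model.

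**Inputs**
- Correlation ρ = 0.47: Table 1, TSRQ autonomous scale, 18-month retest.
- n = 40 per arm and two-sided α = 0.05: Proposed Sample Size, stated for the primary outcomes and assumed here for the secondary ones.
- Assumed: equal variances over time (score variance set to 1), no other covariates, one follow-up visit.
- True effect: not given in the article, so varied from 0.2 to 1.0 SD.

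**Variance per patient, in units of the score variance**
- Unadjusted change: 2(1 − ρ) = 2 × 0.53 = 1.06
- Follow-up score alone: 1.00
- With the screening score as covariate: 1 − ρ² = 1 − 0.2209 = 0.779
- Ratio, adjusted to change: (1 + ρ)/2 = 1.47/2 = 0.735, a reduction of 26.5%; 80 × 0.735 = 58.8 patients

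The same variances come from generalised least squares with visits at screening, 3, 6 and 12 months under compound symmetry. An unconstrained group-by-time change contrast has variance 1.06. A model with a common screening mean in both arms has 0.779.

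**Power**, by normal approximation: Φ(d / (√V × √(2/40)) − 1.96), where V is the variance above. For d = 0.5:
- Change: √1.06 × √0.05 = 0.2302; 0.5/0.2302 − 1.96 = 0.21; power 58.4%
- Adjusted: √0.779 × √0.05 = 0.1974; 0.5/0.1974 − 1.96 = 0.57; power 71.7%

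| True effect (SD) | Change | Adjusted | Loss (points) |
|---|---|---|---|
| 0.2 | 13.8% | 17.2% | 3.4 |
| 0.3 | 25.6% | 33.0% | 7.4 |
| 0.4 | 41.2% | 52.7% | 11.5 |
| 0.5 | 58.4% | 71.7% | 13.3 |
| 0.6 | 74.1% | 86.0% | 11.9 |
| 0.7 | 86.0% | 94.4% | 8.4 |
| 0.8 | 93.5% | 98.2% | 4.7 |
| 1.0 | 99.1% | 99.9% | 0.8 |

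The noncentral t gives 57.3% and 70.6% at 0.5 SD, the same gap. With 36 per arm (10% attrition) the loss at 0.5 SD is 13.1 points.

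**Sensitivity to the correlation.** If the effect is such that the adjusted analysis has 80% power, the loss is 12.9 points at ρ = 0.47, 9.3 at 0.60, 6.7 at 0.70 and 4.3 at 0.80. The last three correlations are assumed values.

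**The case against.** The strongest reply is that this is one condensed sentence in a journal article. It covers several outcomes, gives no random effects, visit terms or covariance structure, and includes an open category of clinical and demographic characteristics. The screening score is not expressly excluded, and the full covariate list may stand in a document that is not shown. Nor must change mean a raw difference. The primary analysis section speaks of score changes in connection with longitudinal trajectories that include the preintervention visit, and a repeated-measures model with a common baseline mean would lose nothing.

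Part of this stands: the loss is conditional on how the model is fitted. But the sentence does fix the form of the outcome and does list adjusters, and a motivation score is not naturally a clinical or demographic characteristic. An unconstrained group-by-time contrast would not avoid the loss either.

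The reply is also right about the inputs. The 0.47 is an 18-month figure for one scale, whereas follow-up here is 3 to 12 months. It says nothing about self-efficacy. Table 1 also gives 0.34, but for controlled items, and these are not the listed outcome. The planned model has other covariates, and Table 1 reports a correlation of 0.58 between the TSRQ and medication adherence, so the residual variance under the actual model is unknown.

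A reader might also infer that the group coefficient averages in the screening visit and so recovers only three quarters of the effect. That would require a repeated-measures model with no time-by-group term, and a summary sentence that leaves the term out does not establish this.

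**Conclusion.** The concern holds as a point about precision. As written, the model takes change as the outcome and does not name the construct's screening score. If change is analysed without it, or through an unconstrained group-by-time contrast, the variance is 1.06 instead of 0.78 of the score variance at a correlation of 0.47. This assumes equal variances and no other covariates. Under equal variances the direction holds for every correlation below 1; the size shrinks as the correlation rises.

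A reader might infer a fixed cost of about 13 power points. The documents do not support that. The figure needs a true effect near 0.5 SD, which the article never gives, and it is close to the maximum for one visit at this correlation. The supportable statement is about 1 to 13 points for effects of 0.2 to 1.0 SD, with no figure available for self-efficacy.

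A reader might also infer bias. Randomisation keeps the unadjusted change comparison unbiased on average. What is lost is precision in a secondary outcome for which no power is claimed.

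**What to change.** In Statistical Analyses, Secondary Outcome Measures, state that the model for each construct includes that construct's screening score as a fixed covariate, with visit, group and visit-by-group terms over the visits at 3, 6 and 12 months. Equivalently for precision, specify a repeated-measures model in which screening is an outcome visit with a common mean in both arms.

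The dependent variable may remain the change. Once the screening score is a covariate, moving it to the other side of the equation only shifts its coefficient by one, so the group difference at a given visit is the same for change and follow-up score.

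The cost is one sentence and one degree of freedom per model, with no new data, since Table 1 already schedules the construct measures at screening. That row names an instrument only for autonomous self-regulation, so the sentence should also name the self-efficacy measure and confirm that it follows the same schedule. According to the Results section, only baseline data were being analysed at the time of the article, so the change could still be made before outcome analysis.

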#### Exploratory Outcomes Measures

In exploratory analyses, change in eGFR, variability of calcineurin trough levels, and 24-hour ambulatory BP will be compared between the two groups using pooled *t* tests (or nonparametric tests, as appropriate). If the end-of study outcomes for eGFR and 24-hour BP are missing, they will be imputed using multiple imputation methods. Further, frequency distributions of adverse events and serious adverse events will be determined, and proportions for the SMASK versus SC groups will be compared using Chi-square analyses.

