**Methods:**

This two-arm, 6-month, phase II single-site efficacy RCT will involve 80 kidney transplantation recipients. Participants will be randomly assigned to the SMASK intervention arm or control arm. SMASK includes multilevel components: automated reminders from an electronic medication tray; tailored text messages and motivational feedback, guided by the self-determination theory; and automated summary reports for providers. Evaluations will be conducted preintervention, at 3 and 6 months, and posttrial at 12 months. Specific aims are to test the hypotheses that compared to standard care, the SMASK cohort will demonstrate significantly improved changes at 3, 6, and 12 months in the primary outcome variables medication adherence (proportion with electronic monitor-derived score >0.90) and blood pressure control (proportion meeting and sustaining adherence to the Kidney Disease Improving Global Outcomes [KDIGO] guidelines for blood pressure control); the secondary outcome variables provider adherence to KDIGO guidelines, measured by timing of medication changes and changes in self-determination theory constructs; and the exploratory outcome variables estimated glomerular filtration rate, variability in calcineurin inhibitor trough levels, and proportion of patients meeting and sustaining the 24-hour ambulatory blood pressure below 130/80 mm Hg. After the 6-month evaluation, interviews with a random sample of SMASK subjects (n=20) and health care providers (n=3-5) will assess user reactions including acceptability, usability, and aids/barriers to sustainability. Data from the RCT and interviews will be triangulated to further refine and optimize SMASK and prepare for a multisite effectiveness RCT.

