### Study Participants

The participants are adult kidney transplant recipients with uncontrolled hypertension who have met the inclusion/exclusion criteria. Potentially eligible study patients were identified through weekly data extractions from the appointment database.

The inclusion criteria for participants were age >18 years (male or female), first- or second-time recipient of a functioning solitary kidney transplantation performed 6 weeks to 60 months earlier, legally competent, assent provided by the transplant physician so that the patient is able to participate, patient prescribed ≥3 medications for immunosuppression and hypertension, electronic pill tray–based medication adherence score <0.85 across a 1-month screening period, uncontrolled systolic hypertension (SBP ≥130 mm Hg) at the screening visit and baseline evaluation (following 1-month medication monitoring period), and 24-hour ambulatory SBP ≥130 mm Hg following the medication monitoring period.

The exclusion criteria were severe cognitive impairment/dementia; inability to self-administer medications, self-measure BP, or use a mobile phone; poor cellular coverage at home; inability to speak, hear, or understand English; history of psychiatric illness or substance abuse; planned pregnancy; and vulnerable populations such as pregnant or nursing women, prisoners, and institutionalized individuals.

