**Exploratory outcomes**								
	eGFR^i^	GFR^j^ estimation equations [55,56]	✓	✓	✓	✓	✓	✓
	Ambulatory BP	24-h ambulatory BP with SpaceLabs 90207		✓			✓	✓

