#### Exploratory Outcome Measures

These will include changes in estimated glomerular filtration rate (eGFR) and variability of CNI trough levels (%cv). CNIs have a well-described high inter- and intrapatient variability as well as a narrow therapeutic index. For these reasons, among others, therapeutic drug monitoring of CNI is the standard of care in solid organ transplantation and guides all CNI titrations [67,68]. Changes in the 24-hour ambulatory BP will also be examined.

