### Proposed Sample Size

To evaluate SMASK treatment efficacy, 80 patients will be recruited and randomly assigned to either SMASK or SC. The primary outcomes of aim 1 include the proportion of patients with >0.90 medication adherence scores (based on the date/time stamped scores from the electronic trays) and proportion of patients meeting and sustaining adherence the KDIGO guidelines for clinic-based SBP control (<130 mm Hg). In intent-to-treat (ITT) analysis, with 40 patients per group, a two-sided Chi-square test (α=0.05) will have >90% power to detect a difference of 35% in proportions of those who are medication adherent (or meeting and sustaining adherence to the KDIGO BP guidelines) in the SMASK group compared to those in the SC group at the 3-month time point. A difference of 35% in medication adherence between the groups would be considered clinically relevant and warrant changes in clinical practice. Conservative estimates for medication adherence and expected BP control proportions will be used for power calculations. This approach was taken with a small pilot study, and CIs on effect sizes were quite large. Medication adherence observed in the SMASK 3-month feasibility study was 89% (versus 0% in control group; N=19). For the clinic resting BP control, we observed that 90% versus 10% of the participants controlled BP in the SMASK and control groups, respectively. Overall attrition was 10% in the intervention group [69].

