### Statistical Analyses

#### Primary Outcome Measures

The ITT analysis set will be determined in accordance with the International Conference on Harmonization E9 Guideline “Statistical Principles for Clinical Trials” [70] and will include all randomized subjects. For all subjects included in the ITT analysis set, all available data points will be included in the model. We chose a mixed-effects model approach because this method is a standard method in RCTs and can handle missing data and account for correlated data such as repeated measurements within patients or patients clustered within providers [71-73].

We propose a two-level analysis strategy: Our primary analysis will include the simple mixed-effects model containing the fixed time and intervention group, time, and time-by-intervention as primary independent variables (fixed effects) and MD as a random effect to account for clustering. The main analysis will compare the two intervention groups (SMASK vs SC) at the primary time point outcome at 3 months. We will estimate medication adherence score changes and changes in resting and 24-hour BP for each subject over the trial (preintervention and 1, 3, 6, and 12 months) and the within-subject longitudinal trajectories (eg, slopes) and summarize the mean longitudinal trajectory within each group. Intraclass correlations and variance estimates will be obtained for the efficacy outcomes and covariance structure of the longitudinal scores to determine the sample size (and hence adequate power) for a future effectiveness RCT.

In secondary/exploratory analysis for aim 1 outcomes, the potential influence of *a priori* specified covariates on these models will be explored, including self-determination theory tenants, demographic and clinical characteristics, and comorbidities. In an additional exploratory analysis, effect modifications of covariates will be examined through inclusion of covariate-by-group interaction terms in the multivariable models.

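### Change in 24-hour ambulatory BP is compared without adjustment for a baseline that every entrant must have: unbiased, but less precise than a free baseline-adjusted comparison

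*Protocol article*

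**What the plan says.** Under Statistical Analyses, Exploratory Outcomes Measures, the protocol article states that "change in eGFR, variability of calcineurin trough levels, and 24-hour ambulatory BP will be compared between the two groups using pooled" t tests, with nonparametric tests as the alternative. No covariate is named. The Exploratory Outcome Measures paragraph confirms that change is the quantity of interest: "Changes in the 24-hour ambulatory BP will also be examined". Missing end-of-study 24-hour BP is to be multiply imputed.

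The baseline exists. The Table 1 row "24-h ambulatory BP with SpaceLabs 90207" is ticked at baseline, 6 months and 12 months, and the inclusion criteria require "24-hour ambulatory SBP ≥130 mm Hg following the medication monitoring period".

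Two other places touch the same outcome. The abstract gives a responder form, "proportion of patients meeting and sustaining the 24-hour ambulatory blood pressure below 130/80 mm Hg". The Primary Outcome Measures analysis section says it will estimate "changes in resting and 24-hour BP for each subject over the trial (preintervention and 1, 3, 6, and 12 months"). The model described there has group, time, their interaction and a physician random effect, with no baseline covariate. Covariates are explored only for the aim 1 outcomes, and baseline ambulatory BP is not named among them.

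**The concern.** A change score subtracts the baseline in full, whatever the actual slope of follow-up on baseline. When that slope is below 1, part of the baseline's own variation stays in the change score as noise. Regressing follow-up on baseline estimates the slope and removes that noise, using data already in hand.

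The stake is precision. BP monitors for home use go to the intervention arm only (Mobile Health Intervention; Blinding), so ambulatory BP is the only out-of-clinic BP available in both arms. It is a natural check on the clinic SBP result in a trial whose participants know their assignment. With at most 80 patients, precision that costs nothing is worth having.

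**Working it through.** **Inputs.** From the article: 40 per arm, two-sided α = 0.05 (Proposed Sample Size), and an entry cutoff of 130 mm Hg on 24-hour SBP (Study Participants). Not in the article: the SD of 24-hour SBP, its baseline-to-follow-up correlation r, and the position of the cutoff in the unselected distribution. These are assumed and varied below.

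**The plan's own figure.** The only stated power concerns the primary proportions: "with 40 patients per group, a two-sided Chi-square test (α=0.05) will have >90% power to detect a difference of 35% in proportions". No control proportion is fixed there. The normal-approximation power at 40 per arm is 99.3% for 0% vs 35%, 95.4% for 10% vs 45%, 91.4% for 20% vs 55% and 90.2% for 25% vs 60%. Its minimum is 89.4%, at 32.5% vs 67.5%. The figure therefore reproduces, falling marginally short only for mid-range control rates. This point does not affect it.

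**Step 1: equal variances, no truncation.** Per-patient variance is 2σ²(1-r) for the change score and σ²(1-r²) after adjustment. The ratio is (1-r²)/[2(1-r)] = (1+r)/2, so the reduction is (1-r)/2.

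| assumed r | 0.3 | 0.5 | 0.6 | 0.7 | 0.8 | 0.9 |
|---|---|---|---|---|---|---|
| reduction | 35% | 25% | 20% | 15% | 10% | 5% |

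Simulation with N = 80 gave 24.6% at r = 0.5 and 15.7% at r = 0.7.

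**Step 2: the entry cutoff.** Let k be the share of baseline variance that remains after selection. With follow-up = r × baseline + error, the change score has variance proportional to (1-r)²k + (1-r²), and the adjusted comparison 1-r². The reduction is (1-r)k/[(1+r) + (1-r)k]. For a normal baseline cut at c SDs from its mean, k = 1 + cλ - λ², where λ is the normal density at c divided by the upper tail area.

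| cutoff, relative to unselected mean | k | r = 0.5 | r = 0.6 | r = 0.7 |
|---|---|---|---|---|
| 2 SD below | 0.886 | 22.8% | 18.1% | 13.5% |
| 1 SD below | 0.630 | 17.3% | 13.6% | 10.0% |
| at the mean | 0.363 | 10.8% | 8.3% | 6.0% |

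Here r is the correlation before selection. Example: r = 0.5, k = 0.630 gives 0.315/(1.5 + 0.315) = 17.3% (k unrounded). Simulation with the cutoff at the mean gave 8.4% (r = 0.5) and 5.5% (r = 0.7), a little below the formula.

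**Step 3: in power terms.** Take an effect for which the t test has 80% power, so the standardised effect is 1.96 + 0.84 = 2.80. A 17.3% reduction gives 2.80/√0.827 = 3.08, about 87% power. A 6.0% reduction gives 2.80/√0.940 = 2.89, about 82%. Without truncation the values would be 90%, 88% and 86% at r = 0.5, 0.6 and 0.7.

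**Step 4: cost of adjustment.** One covariate inflates the variance by about 1/76 = 1.3% at N = 80. Three single-degree-of-freedom terms (baseline, race as two groups, gender) cost at most about 3/74 = 4.1% if race and gender predict nothing. The Step 2 range of 17.3% to 6.0% then becomes 1 - 0.827 × 1.041 = 14% to 1 - 0.940 × 1.041 = 2%.

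**The case against.** The strongest reply is that nothing here is invalid. The arms are randomised, the outcome is labelled exploratory, no power is claimed for it, and a condensed article may leave covariates to the analysis plan. Validity and status stand as stated. The last argument does not carry, because the article names a specific unadjusted test rather than staying silent.

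A second reply is that the mixed-model section also covers 24-hour BP. It does, but with a free group effect at the preintervention time its group-by-time contrast is again essentially a difference in change, so it does not supply the adjustment. It also lists 1 and 3 months, when Table 1 schedules no ambulatory recording.

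Three stronger readings are tempting and are not supported:

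- A reader might infer that the plan gives up 15% to 25% of the variance. That is only r = 0.7 to 0.5 with equal variances, which the article does not supply. The entry criterion that guarantees the baseline also truncates it and reduces the gain.
- A reader might infer that selecting high baselines biases the comparison through regression to the mean. Both arms are selected alike, so it adds noise and no bias.
- A reader might infer that clinic BP is assessed unblinded. The Blinding section says that assessors of primary and secondary outcomes are blinded. Only participants are stated to know their arm.

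**Conclusion.** The point holds as a minor, free improvement. The named test for change in 24-hour ambulatory BP ignores a baseline that is scheduled and required for entry, and a baseline-adjusted comparison is asymptotically never less precise.

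The size is uncertain because the article gives no SD or correlation. Under equal variances the reduction runs from 35% to 5% over r of 0.3 to 0.9. With truncation it is roughly 6% to 17% for unselected r of 0.5 to 0.7 and a cutoff between the unselected mean and 1 SD below it, assuming a normal baseline and a linear relation. At the low end the gain is small once degrees of freedom are paid for. Neither the validity of the comparison nor the stated primary power is in question.

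**What to change.** In Exploratory Outcomes Measures, replace the t test for 24-hour ambulatory BP by a linear model of 24-hour SBP at a named visit (6 months, and separately 12 months). The terms are arm, the pre-randomisation 24-hour SBP recorded after the monitoring period, and the stratification factors race and gender. Fit it within each imputed data set and combine the results, with arm and baseline 24-hour SBP in the imputation model.

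Three places need alignment at the same time:

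- The mixed-model paragraph should say how its estimate of 24-hour BP change relates to this model, and should list only visits at which Table 1 schedules the recording.
- The baseline recording should be identified. The Recruitment section describes the monitor being worn before the 1-month screening period, while the inclusion criterion refers to a recording after it.
- The abstract's proportion below 130/80 mm Hg should be reconciled with the change outcome, since a linear model of SBP does not estimate it.

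The cost is wording and a few degrees of freedom. No new data are needed.

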### Active Trial Evaluations and Follow-Up Phase

All subjects will be followed up for an additional 6 months following the 6-month active trial. Patients will continue to attend the clinic at a frequency determined by the provider. At 1, 3, 6, and 12 months after randomization into the SMASK or SC group, subjects will be assessed on medication adherence using medication possession ratio checks, clinic resting BPs, and completion of a brief set of questionnaires including measures to assess self-determination theory tenants of autonomous self-regulation and self-efficacy (Table 1). Providers are assessed on adherence to BP management protocols and goals. The timeliness and appropriateness of medication changes will be evaluated according to KDIGO guidelines across both groups at the conclusion of the study.

**Table 1 table1:** List of measures and evaluation time points.

Outcome variables		Measurements/instruments used	Screening	Baseline	1 month	3 months	6 months	12 months

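### Change in eGFR is tested by an unadjusted pooled t test, although repeated pre- and post-randomisation values would support a more precise baseline-adjusted repeated-measures analysis

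*Protocol article*

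**What the plan says.** - **Analysis.** Exploratory Outcomes Measures (Statistical Analyses) says "change in eGFR, variability of calcineurin trough levels, and 24-hour ambulatory BP will be compared between the two groups using pooled" t tests, with a nonparametric alternative. No covariate and no time point are named.
- **Missing data.** The same paragraph says: "If the end-of study outcomes for eGFR and 24-hour BP are missing, they will be imputed using multiple imputation methods". No rule is given there for other visits, and the imputation model is not described.
- **Schedule.** Table 1 ("List of measures and evaluation time points") has an eGFR row, "estimation equations [55,56", ticked at screening, baseline and 1, 3, 6 and 12 months. That is two values before randomisation and four after it.
- **Status.** Exploratory Outcome Measures introduces the group with "These will include changes in estimated glomerular filtration rate (eGFR) and variability of CNI trough levels (%cv".
- **Time points of interest.** The Abstract (Methods) lists eGFR among the outcomes whose changes are hypothesised to improve at 3, 6 and 12 months.
- **The article's reasoning elsewhere.** For the primary outcomes, mixed models are chosen because they "can handle missing data and account for correlated data such as repeated measurements within patients or patients clustered within providers". The secondary outcomes are also given mixed models.

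**The concern.** eGFR is scheduled more often than the treatment questionnaire or ambulatory pressure, and it is the kind of repeated, possibly incomplete measure for which the article chose mixed models. It is nevertheless compared by a raw change score. Subtracting baseline fixes the regression coefficient of follow-up on baseline at 1. When the two are imperfectly correlated and have equal variance, the best coefficient is below 1, so the subtraction adds baseline noise. A second pre-randomisation value, which could reduce that noise, has no stated role.

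What is at stake is precision in a trial of 40 per arm, and consistency with the article's own reasoning. The Discussion (limitations) names graft function as a subject for later longitudinal studies, so a tighter estimate here would be useful to them. Neither bias nor the type I error rate is in question.

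**Working it through.** **Plan's own figures.** The article gives no SD, correlation or power for eGFR, so there is nothing to reproduce for this outcome. Its only power statement ("with 40 patients per group, a two-sided Chi-square test (α=0.05) will have >90% power to detect a difference of 35% in proportions") concerns the primary proportions. It comes out at 89.4% to 97.6% for control rates from 0.10 to 0.60, close to what is claimed, and has no bearing on eGFR.

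**Inputs.** From the article: 40 per arm, and eGFR times taken as −1, 0, 1, 3, 6 and 12 months (the screening period is one month). Assumed: unit SD at each visit and a correlation ρ of 0.6 to 0.9 between baseline and the follow-up value.

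**Step 1, one baseline value.** Per-patient variance entering the group contrast:
- change score: 2(1 − ρ)
- adjusted for baseline: 1 − ρ²
- ratio: (1 − ρ²) / [2(1 − ρ)] = (1 + ρ)/2

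**Step 2, mean of screening and baseline, compound symmetry.** The mean has variance (1 + ρ)/2 and covariance ρ with follow-up. The adjusted variance is therefore 1 − 2ρ²/(1 + ρ), and its ratio to the change score is (1 + 2ρ) / [2(1 + ρ)].

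| ρ | Change score | One baseline | Saving | Mean of two | Saving |
|---|---|---|---|---|---|
| 0.6 | 0.800 | 0.640 | 20% | 0.550 | 31% |
| 0.7 | 0.600 | 0.510 | 15% | 0.424 | 29% |
| 0.8 | 0.400 | 0.360 | 10% | 0.289 | 28% |
| 0.9 | 0.200 | 0.190 | 5% | 0.147 | 26% |

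**Step 3, other covariance structures (12-month contrast).**
- *Continuous AR(1).* A second, earlier value adds nothing to baseline. If the mean is used as a single covariate, the adjusted variance is 1 − ρ²m, where m = (1 + ρ^(1/12))/2. At ρ = 0.6, m = 0.979 and the variance is 0.648, against 0.800 (saving 19%). At ρ = 0.9, m = 0.996 and the variance is 0.194, against 0.200 (saving 3%).
- *Random intercept and slope* (intercept variance 0.8 or 0.9, residual variance 0.2 or 0.1, slope SD 0.3 per 12 months). The change score gives 0.490 and 0.290. One baseline gives 0.450 and 0.280 (savings 8% and 3%). Both pre-randomisation values give 0.386 and 0.244 (savings 21% and 16%).

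**Step 4, what this means at 40 per arm.** The difference detectable with 80% power is (1.96 + 0.84)·√(2v/40), where v is the variance above. At ρ = 0.8 it is 0.396 SD for the change score, 0.376 SD with one baseline and 0.337 SD with two under compound symmetry. Over ρ from 0.6 to 0.9, an effect that the change score detects with 80% power would be detected with 82% to 88% power (one baseline) or 90% to 92% (two, compound symmetry).

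**Step 5, the intermediate visits.** With complete data, a model with free visit-by-group terms gives a 12-month contrast that is essentially the baseline-adjusted comparison at 12 months. The 1-, 3- and 6-month values add almost nothing to it. They help mainly when the later value is missing, because the patient's observed visits then inform the contrast directly.

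**The case against.** The strongest case against is that this is optional advice. A t test on change is valid in a randomised comparison, eGFR is exploratory, and the Discussion itself says the study is too short to show a significant gain in graft function. No stated decision depends on this test. All of that stands and limits the weight of the point.

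Three stronger readings are tempting, and the article does not support them.

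- *Four of the six eGFR values are thrown away.* A reader might infer this from the reference to end-of-study outcomes in the imputation sentence. That sentence concerns missing data, and the analysis sentence names no time point. The Abstract points to changes at 3, 6 and 12 months. If each is tested, only one pre-randomisation value and the 1-month value have no role.
- *Imputation ignores the intermediate visits.* The imputation model is not described and could include them. Its detail may properly sit in a document not shown here.
- *A longitudinal model would cut the variance far more.* Larger savings arise if a straight-line divergence between arms over 12 months is assumed. The intervention stops at 6 months, so linearity is doubtful, and a model with visit-by-group terms does not deliver those savings.

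None of this removes the core. On either reading of the time point, the named test is an unadjusted change score, and adjustment was more precise under every structure examined.

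**Conclusion.** The point holds as a minor matter of efficiency. The article specifies a valid but needlessly imprecise test for eGFR, although the data for a better one are already scheduled and the article gives the rationale itself.

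On equal variances and an assumed correlation of 0.6 to 0.9, adjustment for one baseline value saves about 5% to 20% of the variance. Averaging two saves about 26% to 31% under compound symmetry. The saving can be as low as about 3% under AR(1) with high correlation, or with random slopes and a single baseline. These figures describe complete data and rest on assumed correlations. The added value of the intermediate visits lies mainly in handling missing values and was not quantified.

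The point is specific to eGFR. Ambulatory pressure ("24-h ambulatory BP with SpaceLabs 90207") shares the same sentence but is scheduled only at baseline, 6 and 12 months.

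**What to change.** Replace the eGFR part of the exploratory analysis with a mixed model for repeated measures on the 1-, 3-, 6- and 12-month values. Include visit, group and visit-by-group terms, within-patient correlation, and the mean of screening and baseline eGFR as covariate, preferably with a visit-specific coefficient. Report the 3-, 6- and 12-month group contrasts with confidence intervals, matching the Abstract. Keep the t test on change as a sensitivity analysis, state its time point, and say whether the imputation model uses the intermediate values.

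The cost is a few sentences of analysis text and slightly more modelling. No visit, sample or patient is added. The change should be dated and made before eGFR is compared by arm.
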